### PET Imaging Acquisition

Integrated PSMA PET/MRI is preferred with the goal of achieving co-registered PSMA PET and MR images with high spatial fidelity for planning and assessing response to treatment. PSMA PET/CT plus mpMRI are also allowed within the protocol if there is an unavailability of a PET/MRI scanner. We have previously demonstrated the value of early dynamic PET imaging in the identification of intra-prostatic lesions and will incorporate both dynamic and delayed PET imaging (56).

The evening before each PSMA PET examination, patients will be asked to take 30 ml of milk of magnesia, an over-the-counter laxative, which will be provided. Patients should be NPO overnight prior to the exam (~12 h). The bladder should be comfortably full and the rectum as empty as possible prior to image acquisition.

For dynamic PET imaging, the participants will be injected with 3–4 MBq/kg (up to a maximum 400 MBq) of ^18^F-PSMA-1007. Dynamic PET acquisitions will start immediately prior to ^18^F-PSMA 1007 injection and will be acquired simultaneously with the cross-sectional pelvic MR images (for PET/MRI) or CT images (for PET/CT). Dynamic PET acquisition will cover the whole prostate up to the iliac crest. An image-derived arterial time–activity curve required for kinetic analysis of dynamic PET data will be acquired from an internal iliac artery to generate parametric maps. Starting at the injection of ^18^F-PSMA-1007 as a bolus into an antecubital vein, the dynamic PET scan will be acquired over 22 min with seven framing intervals: 10, 20, 40, 60, and 180 s. Early time standardized uptake (SUV_early_) in g/ml will be measured as the average of the last four dynamic PET volumes (10–22 min post-injection). The acquired dynamic volumes will be analyzed to generate parametric maps of the whole prostate, including influx rate constant (K_1_), efflux rate constant (k_2_), binding rate constant (k_3_), dissociation rate constant (k_4_), net uptake rate constant from plasma (K_i_), and distribution volume (DV) maps by deconvolving the arterial time–activity curve from tissue time–activity curve using a flow-modified two-tissue compartment (F2TC) model. After dynamic pelvic PET, participants will be allowed to get up and take a break/empty their bladder prior to the acquisition of late uptake PSMA-1007 PET images (60–120 min post-injection). For PET/CT, the PET images will be acquired with corresponding axial CT images obtained (for anatomic correlation and attenuation correction).

For PET/MRI, a whole-body MRI scout scan (to plan the study) and B0 homogenization using gradient enhancement (HUGE) acquisition (to correct for truncation of arms) will be acquired first. In both acquisitions, the table moves continuously for approximately 1 min as it scans the subject from head to thigh. Whole-body PET/MRI is acquired in multiple bed positions. For men of average height, 5 overlapping table positions will be used, with taller subjects requiring an additional table position. At each table position, a 5-min PET acquisition will be acquired along with simultaneous MRI consisting of MRI-based attenuation correction, coronal T2-weighted fast spin-echo with Short-TI Inversion Recovery (STIR) sequence during flat breathing, and axial Half-Fourier Acquisition Single-shot Turbo spin-Echo (HASTE) single-shot T2-weighted sequence. For thoracic and abdominal table positions, the HASTE MRI will be captured over 4 breath-holds of 14 s. If unable to do so, these can be done with flat breathing only.

### Pelvic Multiparametric MRI Acquisition

For men imaged with PET/MRI, the pelvic mpMRI will be acquired after whole-body PET/MRI on the PET/MRI scanner. For men imaged with PET/CT, mpMRI will be acquired as a separate study on a 3T magnetic resonance scanner. The bladder should be comfortably full and the rectum as empty as possible prior to the mpMRI scanning. For mpMRI scout scans, sagittal 2D T2-weighted, coronal 2D T2-weighted MRI, axial 3D T2-weighted, and 2D axial diffusion-weighted EPI will be acquired. Prior to a 3D DCE T1-weighted MRI, a radiologist or designate will administer an intravenous injection of GADOVIST^®^ 1.0 (Gadobutrol) with the MEDRAD Injection System (0.1 mmol/kg). Following DCE-MRI, whole-body late gadolinium-enhanced MRI will be acquired with T1-weighted volumetric interpolated breath-hold examination (VIBE) with fat saturation and breath-hold in thoracic and abdominal table positions.

### Primary Endpoint and Sample Size

This will be a single-phase pilot study of 50 patients with a primary endpoint of GI and GU toxicity as measured by CTCAE v5.0.

Unacceptable toxicity will be defined as acute (6 weeks) or intermediate (6 months) grade >3 GI or GU toxicity. The proposed treatment will be deemed too toxic if >30% of patients have unacceptable toxicity. This study tests the hypothesis that acute toxicity is <30% (alpha = 0.05, power = 81%, one-sided, H0: p = .30, HA: p <.30), with an assumed true proportion in this study of 15%. These calculations were done based on a Z test (normal approximation). We will test this assumption with the exact test approach if we do not meet our target accrual of 50 men or the proportion of Grade 3 toxicity is significantly less than 15% (conditions where normal approximation is not met).

Given that the proPSMA study demonstrated that 16% of men with high-risk prostate cancer had extra-prostatic disease beyond regional nodal metastases at initial staging and the fact our population will be a mix of high-intermediate and high-risk men, we will plan to enroll a total of 55 men (22). Those men with extra-prostatic spread beyond regional pelvic lymph nodes on their pretreatment PSMA PET imaging will be treated off protocol at the attending physician’s discretion.

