**Figure 2 f2:**
[figure not shown]
Example of focal dose escalation.

**Table 3 T3:** Dose constraints.

Structures and dose constraints (acceptable deviations)			
**Rectum**	V20Gy ≤ 50% (optimal) V28Gy ≤ 15% (20%) V32Gy ≤ 10% (15%) V35Gy ≤ 2 cc (4 cc) V38Gy ≤ 1 cc Dmax ≤ 40.6 Gy	**Bladder**	V20Gy ≤ 50% (optimal) V28Gy ≤ 15% (20%) V32Gy ≤ 10% (15%) V38Gy ≤ 6 cc V39.5Gy ≤ 2 cc
**Rectum_PRV**	Dmax ≤ 45 Gy	**Bladder_PRV**	Dmax ≤ 46 Gy (optimal)
**Urethra_PRV**	Dmax ≤ 52 Gy D10% ≤ 47.2 Gy D50% ≤ 42 Gy (optimal)	**Penile Bulb**	V20Gy ≤ 40% (90%) V35Gy ≤ 4%
**Bowel_Small**	V25Gy ≤ 20 cc (40cc) V30Gy ≤ 2 cc Dmax ≤ 3 5Gy	**Bowel_Large**	V25Gy ≤ 20 cc (40 cc) Dmax ≤ 38 Gy
**Femur_R and Femur_L**	V28Gy ≤ 5%		

The primary endpoints of the trial will be 6-week and 6-month gastrointestinal (GI) and GU toxicity using the Common Terminology Criteria for Adverse Events version 5.0 (CTCAE v5.0). While other prospective trials have confirmed the safety of an mpMRI-defined intra-prostatic boost with external beam radiotherapy (4, 6), the proposed boost volume in ARGOS/CLIMBER will be based on mpMRI and PSMA PET-targeted PET (17), and thus there is a need to demonstrate the safety of such a multi-modality defined boost volume. Secondary endpoints include Quality of life measured by the Expanded Prostate Cancer Index Composite (EPIC-26) questionnaires and 5-year disease-free survival (DFS) as a composite of BF, patient death, or development of clinical metastases or institution of salvage ADT.

All grade 3 or higher toxicity will be reported to the principal investigator. An independent data and safety monitoring board (IDSMB) will perform a formal interim analysis for safety and toxicity when half of the patients have been accrued or after 1 year, whichever comes first. The study will be discontinued if the projected rate of grade 3 or higher urinary or bowel toxicity exceeds 30%. IDSMB will meet at least annually to review trial data.

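### The primary toxicity event is written as grade >3, but the discontinuation rule at the same 30% limit counts grade 3 or higher, so the article contradicts itself on whether grade 3 events enter the primary test

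*Protocol article*

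**What the plan says.** Primary Endpoint and Sample Size defines the event: "Unacceptable toxicity will be defined as acute (6 weeks) or intermediate (6 months) grade >3 GI or GU toxicity". It then sets the limit: "The proposed treatment will be deemed too toxic if >30% of patients have unacceptable toxicity". The test is specified as "alpha = 0.05, power = 81%, one-sided, H0: p = .30, HA: p <.30", "with an assumed true proportion in this study of 15" per cent, with a Z test on 50 patients. The same paragraph goes on to describe when an exact test would replace the Z test. One condition is that "the proportion of Grade 3 toxicity is significantly less than 15" per cent.

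Study Design, in the text after Table 3, gives the monitoring rules: "All grade 3 or higher toxicity will be reported to the principal investigator", and "The study will be discontinued if the projected rate of grade 3 or higher urinary or bowel toxicity exceeds 30" per cent.

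Table 1 lists acute grade 2+ toxicity in the two five-fraction boost trials: 5% GI in both, and 34% and 20% GU. It gives no separate grade 3 or grade 4 rates.

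**The concern.** The final test and the discontinuation rule share a 30% limit and the same organ systems (GI and GU in one place, bowel and urinary in the other). They differ by one grade. Under the literal primary definition, a patient with grade 3 toxicity and nothing worse counts towards discontinuation but not towards the primary result.

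This is the only endpoint with a stated null hypothesis, alpha and power, and Study Design presents it as the way to show that the combined MRI and PET boost volume is safe. If grade 3 is left out, the test can declare the regimen acceptable while the grade 3 or higher rate is at or above the limit used for monitoring. If the threshold is settled only after the data are seen, the choice could be influenced by the result.

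**Working it through.** **1. The statements side by side**

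| Place | Grade named | Rate attached |
|---|---|---|
| Primary Endpoint and Sample Size, event definition | >3 | limit 30%, planning rate 15% |
| Primary Endpoint and Sample Size, exact-test sentence | 3 | planning rate 15% |
| Study Design, discontinuation rule | 3 or higher | limit 30% |
| Study Design, reporting rule | 3 or higher | none |

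The first row excludes grade 3. The two Study Design rows include it. The exact-test sentence is best read as shorthand for the endpoint, and it too points to grade 3 being counted.

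**2. The plan's own power figure**

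Inputs from the sample-size section: n = 50, p0 = 0.30, p1 = 0.15, one-sided alpha 0.05, Z test.

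Power = Φ{[(p0 − p1) − 1.645·√(p0(1−p0)/n)] / √(p1(1−p1)/n)}

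- √(0.30 × 0.70 / 50) = 0.0648
- √(0.15 × 0.85 / 50) = 0.0505
- (0.15 − 1.645 × 0.0648) / 0.0505 = 0.859
- Φ(0.859) = 80.5%, against 81% stated.

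The figure reproduces to within rounding. The grade does not enter the formula, so it is the same under either threshold.

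**3. The rejection region**

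The Z test rejects when the count is below 50 × 0.30 − 1.645 × √(50 × 0.30 × 0.70) = 9.67, that is, at 9 or fewer events in 50. By the exact binomial this region has:

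- P(X ≤ 9 | 0.30) = 0.040, the exact alpha. With 10 events allowed it would be 0.079.
- P(X ≤ 9 | 0.15) = 0.791, the exact power.

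**4. What the threshold does to the conclusion**

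The documents do not say what share of patients with grade 3 or higher toxicity reach grade 4-5. That share is an assumption, shown here over a range. The grade 4-5 rate is the grade 3 or higher rate times the share. Each entry is P(X ≤ 9 of 50), the probability that the test declares the regimen acceptable.

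| True grade 3 or higher rate | Grade 3 counts | Only grade 4-5 counts, share 10% | Share 25% | Share 50% |
|---|---|---|---|---|
| 30% | 4.0% | >99.9% (rate 3%) | 99.6% (7.5%) | 79.1% (15%) |
| 40% | 0.08% | >99.9% (4%) | 97.5% (10%) | 44.4% (20%) |

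**5. Is 15% plausible as a grade 4-5 rate?**

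In the five-fraction boost trials of Table 1, 15% would be 15/34 = 44% to 15/20 = 75% of the whole acute grade 2+ GU rate, and three times the 5% grade 2+ GI rate. That is implausible for the two highest grades. It is not excluded, because a grade 2+ rate is only an upper bound on any higher grade.

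**The case against.** The strongest reply is that this is a single lost symbol. One character stands against two explicit statements and the shorthand in the exact-test sentence, and ≥ may have been lost in typesetting or in reading the PDF. The sign ≤ survives in Table 3, but ≥ appears nowhere in the text, so its survival is untested. This stands as an explanation of the cause. It does not remove the contradiction, because the text as given says >3 and nothing corrects it.

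It can also be said that safety monitoring may reasonably be more sensitive than the final test. That is true in general, but the article gives no sign that a difference was intended.

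A reader might infer more than the documents support:

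- **That there are three competing definitions.** There are two. The exact-test sentence is shorthand for the endpoint.
- **That Table 1 proves 15% cannot be a grade 4-5 rate.** It gives only grade 2+ rates. The figures cited are also acute, from boosts defined on MRI alone, whereas this endpoint extends to 6 months and the boost uses PET as well.
- **That the regimen could pass with any number of grade 3 events.** The discontinuation rule counts grade 3. Assume 25 evaluable patients at the interim and a projected rate equal to the observed rate. The rule then triggers at 8 or more events: P(X ≥ 8 of 25 | 0.40) = 0.85. The protection is partial, since at a true rate of 30% the same calculation gives 0.49.
- **That one trial could be stopped at the interim and then pass at the end.** That sequence cannot occur in one trial.
- **That the sample size is wrong.** It is not affected.

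**Conclusion.** The point holds as an internal contradiction in the definition of the primary event, most likely a slip for ≥3. The text does not show a deliberate choice to disregard grade 3 toxicity.

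Followed literally, the final test would have little ability to detect an excess of grade 3 toxicity. At a true grade 3 or higher rate of 30%, the chance of declaring the regimen acceptable rises from 4.0% to between 79.1% and over 99.9%, for an assumed grade 4-5 share between a half and a tenth. These figures rest on that assumed share, on the region of 9 or fewer events in 50, and on the trial running to its final analysis. The first is illustrative, but the change of conclusion at 30% does not depend on its exact value within that range.

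The point needs correction before any analysis, because it decides which events the powered test counts.

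**What to change.** Reconcile the passages so that one grade threshold, in identical words, appears in the definition of unacceptable toxicity, in the hypothesis with its 15% and 30% rates, in the exact-test sentence and in the interim discontinuation rule. The article's other statements point to grade 3 or higher. The sponsor should confirm which threshold was intended and, if it differs from the monitoring threshold on purpose, say so and give the reason for 15% at that grade.

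The cost is a short wording amendment. It needs no further patients or data: all grade 3 or higher toxicity is already to be reported, and the sample size of 50 and the stated power of 81% stay as they are.

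### The primary toxicity endpoint has two unlinked criteria, so 10 to 15 events in 50 men would be neither shown to be below 30% nor deemed too toxic

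*Protocol article*

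**What the plan says.** All of this stands in the protocol article, section Primary Endpoint and Sample Size.

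- Size: "This will be a single-phase pilot study of 50 patients with a primary endpoint of GI and GU toxicity as measured by CTCAE v5.0".
- Event: "Unacceptable toxicity will be defined as acute (6 weeks) or intermediate (6 months) grade >3 GI or GU toxicity".
- Verdict: "The proposed treatment will be deemed too toxic if >30% of patients have unacceptable toxicity".
- Hypothesis: "This study tests the hypothesis that acute toxicity is <30"%, with the design values "alpha = 0.05, power = 81%, one-sided, H0: p = .30, HA: p <.30" and "with an assumed true proportion in this study of 15"%.
- Method: "These calculations were done based on a Z test (normal approximation"), with an exact test held in reserve for short accrual or for a rate well under 15%.

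The section does not say how the verdict sentence and the test combine, or what is concluded when the null is not rejected and the observed rate is 30% or less. The interim rule in Study Design (discontinuation if the projected rate exceeds 30%) governs continuation of the trial and does not settle the final conclusion.

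**The concern.** The two criteria put the burden of proof on opposite sides. The verdict sentence speaks only when the rate is above 30%, so harm has to be shown. The test asks for evidence that the rate is below 30%, so safety has to be shown. Alpha and power belong to the test alone, yet the only sentence that draws a conclusion about the treatment is the other one.

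The article gives demonstrating the safety of a boost volume defined on both mpMRI and PSMA PET as the reason for its primary endpoint. If the observed rate falls between the two cut-offs, the main conclusion is not fixed in advance and could be reported either way once the data are known.

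The two sentences also differ in the event they name. The verdict sentence counts acute or intermediate toxicity, while the test sentence names acute toxicity only.

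**Working it through.** **Inputs.** n = 50, p0 = 0.30, p1 = 0.15, one-sided alpha = 0.05 and a Z test, all from Primary Endpoint and Sample Size. I assume that both criteria are applied to the same count X out of 50.

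**Step 1: reproduce the stated power.** With the null variance in the critical value and the alternative variance in the power:

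Power = Φ[(p0 − p1 − 1.645·√(p0(1 − p0)/n)) / √(p1(1 − p1)/n)]
= Φ[(0.15 − 1.645 × 0.0648) / 0.0505] = Φ(0.859) = 80.5%.

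The protocol states 81%, so this is very probably the test that was planned.

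**Step 2: where the test rejects.** z = (x/50 − 0.30)/√(0.21/50).

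| Events | Rate | z | Z-test p | Exact p |
|---|---|---|---|---|
| 9 | 18% | −1.85 | 0.032 | 0.040 |
| 10 | 20% | −1.54 | 0.061 | 0.079 |

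The Z test and the exact test agree: reject at 9 or fewer. Exact alpha is P(X ≤ 9 | 0.30) = 4.0%, and exact power is P(X ≤ 9 | 0.15) = 79.1%. An unpooled (Wald) Z test would also reject at 10 events (p = 0.039), but its matching power is 90.8%, which is not the stated figure.

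**Step 3: where the verdict sentence applies.** 15/50 is exactly 30%, so more than 30% begins at 16 events. The region that neither criterion covers is 10 to 15 events.

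**Step 4: exact binomial probabilities, n = 50.**

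| True rate | 9 or fewer (test rejects) | 10 to 15 (neither) | 16 or more (too toxic) | 15 or fewer (not too toxic) |
|---|---|---|---|---|
| 10% | 97.5% | 2.5% | <0.1% | >99.9% |
| 15% | 79.1% | 20.7% | 0.2% | 99.8% |
| 20% | 44.4% | 52.5% | 3.1% | 96.9% |
| 25% | 16.4% | 67.3% | 16.3% | 83.7% |
| 30% | 4.0% | 52.9% | 43.1% | 56.9% |
| 35% | 0.7% | 27.3% | 72.0% | 28.0% |
| 40% | 0.1% | 9.5% | 90.4% | 9.6% |

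The last column is the chance of passing if a result that is not too toxic counted as acceptable. The second column is the chance of passing under the test.

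**Step 5: what the edge of the region means.** At 15/50 the exact upper one-sided 95% limit is 42%. That result escapes the verdict sentence although it is compatible with rates well above 30%.

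**The case against.** **One design, not two.** The verdict sentence does not contain the word observed, and the hypothesis follows directly after it. One can read the first as setting the 30% bound and the second as saying how it is tested. On that reading the test gives the verdict and alpha is controlled. This reading is reasonable, but the text does not state it, and it still leaves non-rejection at 30% or less without a stated conclusion.

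**No contradiction.** A reader might infer that the two rules are incompatible. They are not: no count is both 9 or fewer and 16 or more. They are unlinked and leave a middle region without a conclusion, as many one-sided tests against a bound do. They would conflict only if each were read as a two-way verdict.

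**The 57%.** A reader might also infer that the plan has a 57% false-safe rate. The document does not say that a treatment not deemed too toxic is acceptable. The figure also belongs to a true rate of exactly 30%, which the verdict sentence itself does not class as too toxic. It falls to 51% at 31%, 28% at 35% and 10% at 40%. It is the size of a risk that the wording leaves open, not a property of the plan as written.

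**How likely the region is.** If the true rate is 10%, only 2.5% of trials land there. Table 1 gives acute grade 2 or higher rates of 5% (GI) and 20% to 34% (GU) in the two five-fraction boost trials. Higher-grade acute rates cannot exceed these, so true rates of 20% to 30% are not shown to be likely. That stands. Even so, the protocol's own planning rate of 15% gives one trial in five.

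**Left to an SAP.** The wording of conclusions is often left to the SAP. Here, however, the article itself states both a verdict sentence and a test, and what it states does not fit together.

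**Conclusion.** The point holds as a gap between two criteria. With 50 men and a common count, 10 to 15 events fail to show a rate below 30% and are not deemed too toxic. The chance of this is 21% at the assumed 15%, 53% at 20% and 67% at 25%. The stated error rates apply only if the test decides. If passing meant merely not being too toxic, a treatment with a true rate of 30%, 35% or 40% would pass 57%, 28% or 10% of the time, against 4.0%, 0.7% and 0.1% under the test.

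This rests on three assumptions: the verdict sentence refers to the observed proportion, both criteria use the same event, and the test is the null-variance Z test that reproduces the stated power (the exact test gives the same cut-off). The second is not secured by the text, because one sentence counts acute or intermediate toxicity and the other names acute only. The sample size calculation is sound and is not in question.

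**What to change.** Revise the paragraph under Primary Endpoint and Sample Size so that it says:

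1. Toxicity is concluded to be below 30% only if the null of 30% is rejected at one-sided 0.05. With 50 men this means 9 or fewer events (exact alpha 4.0%, exact power 79%), recomputed for the number treated.
2. An observed rate of 30% or less without rejection is reported as acceptable toxicity not shown, with the upper one-sided 95% confidence limit.
3. The verdict sentence and the test use the same event, so that acute or intermediate is reconciled with acute. The sponsor should say which is meant.

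This keeps the sponsor's 30% bound, alpha, test and sample size, and changes no data collection. The cost is one paragraph of wording, settled before the data are seen. The downside for the sponsor is that observed rates of 20% to 30% can no longer be presented as a pass.

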Unique to the ARGOS/CLIMBER protocol is the integration of longitudinal imaging with PSMA-directed PET and mpMRI pretreatment and posttreatment. Serial PSMA PET/MR images will be collected at baseline, 6 months, and 2 years to characterize the imaging response of prostate cancer to treatment and potentially identify imaging biomarkers (including pharmacokinetics, radiomics, and quantitative PET and mpMRI metrics) that predict for 5-year DFS (**Table 4**). Additionally, baseline collection of diagnostic tissue biopsy samples and serial collection of blood and urine over multiple time points (baseline, 6 months, 1 year, and 2 years post-SBRT) will be performed for correlative biologic biomarker analyses with imaging changes, DFS, and toxicity posttreatment. Analysis of prostate biopsy at baseline and 2 years will allow for correlation of histopathology with PSMA PET/MR images. We will investigate whether a negative posttreatment PSMA PET/MRI is correlated with a negative 2-year posttreatment biopsy and long-term disease control (36, 39). We also plan to examine novel clinical prognostic biomarkers (i.e., absolute percentage of Gleason Pattern 4 on biopsy and 4-year PSA response rate) and their correlation with imaging findings and 5-year DFS.

**Table 4 T4:** Schedule of events.

Event	Weeks (week 0 is start of RT)										Q6mo (30–60mo)
	−3	−2	0	1 EOT	3	8 (6 weeks post-RT)	6 months post-RT	12 months post-RT	18 months post-RT	24 months post-RT	
	V1	V2	V3	V4	V5	V6	V7	V8	V9	V10	V11–15
Start alpha antagonists, simethicone	x										
Fiducial marker insertion		x									
Simulation and planning		x									
Treatment (5 fractions q2d, 10–12 days)			x	x							
CTCAE v5.0	x		x	x	x	x	x	x	x	x	x
EPIC-26 questionnaires	x		x	x		x	x	x	x	x	x
PSA and testosterone	x					x	x	x	x	x	
PSMA PET/MRI		x					x			x	
Liquid biomarker collection		x				x	x	x		x	
Transperineal biopsy		x								x	

CTCAE v5.0, Common Terminology Criteria for Adverse Events version 5.0; PSA, prostate-specific antigen; PSMA, prostate-specific membrane antigen.

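### The only hypothesis test is stated for acute toxicity, although the primary event and the 30% limit cover toxicity at 6 weeks or 6 months

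*Protocol article*

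**What the plan says.** Under Study Design, after Table 3, both time points are primary: "The primary endpoints of the trial will be 6-week and 6-month gastrointestinal (GI) and GU toxicity".

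Primary Endpoint and Sample Size then makes three statements in a row:

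- The event: "Unacceptable toxicity will be defined as acute (6 weeks) or intermediate (6 months) grade >3 GI or GU toxicity".
- The limit, applied to that event: "The proposed treatment will be deemed too toxic if >30% of patients have unacceptable toxicity".
- The test: "This study tests the hypothesis that acute toxicity is <30" per cent. The same sentence gives the design values ("alpha = 0.05, power = 81%, one-sided, H0: p = .30, HA: p <.30") and ends "with an assumed true proportion in this study of 15" per cent.

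The method follows: "These calculations were done based on a Z test (normal approximation"). The sample size is 50 men, with 55 enrolled to allow for men found to have spread beyond the pelvic nodes.

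**The concern.** The event and the limit cover two time points, and the test names one. The section itself ties the word acute to 6 weeks and uses intermediate for 6 months, so acute toxicity in the test sentence cannot easily be read as both.

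Two things follow.

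- A test carried out as worded leaves out any man whose first qualifying event appears at 6 months.
- A reader cannot tell which event the 15% and the 81% describe. A composite rate can never be below the rate of one of its components, so the choice matters for power.

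Safety of the boost volume defined on both MRI and PET is the stated reason for the trial, and this is its only hypothesis test. If the tested event is settled after the data are seen, the nominal 5% error rate no longer means much.

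**Working it through.** **Inputs, all from Primary Endpoint and Sample Size:** n = 50, p0 = 0.30, p1 = 0.15, one-sided alpha = 0.05 (z = 1.645), one-sample Z test.

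**Step 1. Reproduce the stated power.** With the null variance in the critical value,

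power = Φ[(p0 − p1 − z·√(p0(1−p0)/n)) / √(p1(1−p1)/n)]

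- √(0.30 × 0.70 / 50) = 0.0648
- √(0.15 × 0.85 / 50) = 0.0505
- (0.15 − 1.645 × 0.0648) / 0.0505 = 0.86, and Φ(0.86) = 80.5%

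This agrees with the stated 81%; 50.6 men would give exactly 81%. The arithmetic is sound, and the open question is which event p describes.

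**Step 2. The cut-off in counts.** With 9 events, z = (0.18 − 0.30)/0.0648 = −1.85, which rejects H0. With 10 events, z = −1.54, which does not. The exact binomial gives the same cut-off: P(X ≤ 9 | 0.30) = 4.0% and P(X ≤ 10 | 0.30) = 7.9%. So the test passes with at most 9 of 50. Read as an observed proportion, the too-toxic rule needs at least 16 of 50.

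**Step 3. Behaviour at a range of true rates.** The documents give no rate of new 6-month events, so the rates above 15% are assumptions.

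| True rate of the counted event | Z-test power | Exact P(X ≤ 9) | P(observed > 30%), i.e. X ≥ 16 |
|---|---|---|---|
| 15% | 80.5% | 79.1% | 0.2% |
| 17.5% | 63.4% | 62.4% | 0.9% |
| 20% | 45.4% | 44.4% | 3.1% |
| 25% | 17.8% | 16.4% | 16.3% |
| 30% | 5.0% | 4.0% | 43.1% |

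**Step 4. If acute toxicity alone is tested.** Let 15% of men have an acute event and a further 15 points have a first event at 6 months, so the composite is 15% + 15% = 30%, at the limit. The acute-only test sees only the 15% and passes with probability 79.1%. A test of the composite would pass with probability 4.0%. The observed >30% rule flags this regimen with probability 43.1%.

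**Step 5. If the composite is tested.** If 15% is the composite rate, power stays at 80.5% (79.1% exact). If 15% is the acute rate, 5 added points bring exact power to 44.4% and 10 added points to 16.4%.

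**Step 6. The two rules can disagree.** As an illustration, take 8 men with an acute event and 9 others with a first event at 6 months. The acute test passes (8 ≤ 9), while the composite is 17/50 = 34%, which the other rule calls too toxic. The article does not say which governs.

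**The case against.** The strongest reply is that acute is a stray word. The limit in the preceding sentence is on the composite and is also 30%. The 15% is described only as an assumed proportion in this study, and the sentence on the exact test compares 15% with the proportion of Grade 3 toxicity, without limiting it to the acute period. On that reading the 81% stands and one word needs correcting. This is plausible and cannot be ruled out, so the power loss is conditional. It does not settle the matter, because no sentence assigns the test or the 15% to the composite.

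Several stronger readings are tempting, and the documents do not support them:

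- *That 6-month harm is ignored.* It leaves the formal test only. The >30% rule counts it and would flag a true composite rate of 35% with probability 0.72. At a true 30%, though, that falls to 0.43, and the rule has no stated error rate.
- *That the power was miscalculated.* It reproduces.
- *That toxicity at end of treatment or week 3 which resolves early is excluded.* Table 4 labels one visit "8 (6 weeks post-RT"), but nothing says that only the grade present at that visit counts. Worst grade up to week 6 fits the wording, and such detail is commonly left to the full protocol.
- *That naming GI and GU toxicity in one place and GI or GU in another is a contradiction.* The first names what is measured, and the second defines the event per man.

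It is also fair to say that 15 points of new 6-month events is a limiting case chosen to show the mechanism. It is not a forecast.

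**Conclusion.** The mismatch is real and sits in the current text: the event and the 30% limit cover 6 weeks or 6 months, while H0, alpha, power and the 15% are stated for acute toxicity. This is a wrongly stated test, not detail lost in condensing a protocol to an article.

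Its size depends on what the 15% means. If it is the composite rate, the numbers stand and only the wording is wrong. If it is the acute rate, the 81% applies to the composite only if no man has a first event at 6 months. Followed literally, the acute-only test would usually pass a regimen whose composite rate sits at the limit, and the separate >30% rule would miss it more often than not (57%, from 100% − 43%). These figures assume 50 evaluable men and the assumed 6-month rates shown above.

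It should be corrected before the data are analysed, because the test decides the trial's only primary objective.

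**What to change.** State H0, HA, the assumed rate and the power for the one composite event per man that the article already defines: 6 weeks or 6 months, GI or GU. Say that this test governs the toxicity conclusion, and how the >30% rule relates to it. Say which event the 15% describes. If it was the acute rate, give an assumed composite rate and restate the power. Report the 6-week and 6-month rates separately as descriptive results.

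As a separate matter, the sponsor must reconcile the grade threshold: the event definition says grade >3, while the exact-test sentence in the same section refers to Grade 3.

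The cost is a few sentences and at most one recalculation. Table 4 already collects CTCAE at both visits, so no new data are needed. The downside is that the stated power may turn out lower than 81%.
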